## **4.6 Equipment and materials**

The following equipment will be used: pulse oximeter (Dixtal Biomédica®) to measure heart rate and peripheral oxygen levels, as well as a digital thermometer to measure body temperature before the intervention. A maternity gown will also be used for the mother, along with a moldable cotton band to contain the newborn next to the mother. These materials will be part of the routine usage in the Neonatal Intermediate Care Unit (UCIN).

The following assessment tools or scales will be used: Silverman-Andersen Scoring System (BSA), Prechtl's Qualitative Assessment of General Movements (GMA), adapted Brazelton' Scale, and the Neonatal Neuromotor Screening (TNN).

Two digital video cameras (Sony®), mounted on tripods, will be used to record the evaluations, one for the hospital setting and the other for the clinic setting. The videos will be transferred to a notebook computer and stored on an external hard drive (HD).

## **4.7 Assessment tools**

### **4.7.1. Prechtl's General Movements Assessment (GMA)**

General movements (GMs) make up the main spontaneous motor repertoire in the first months of a baby's life, being present from nine weeks of gestational age until approximately twenty weeks of postnatal life. They involve fluent and graceful movements with variable sequences of the neck, trunk, upper extremities, and lower extremities (PRECHTL, 1990; EINSPIELER; PRECHTL, 2005; EINSPIELER; PEHARZ; MARSCHIK, 2016). The presence, quality, and intensity of these movements provide information about the functional integrity of the newborn's central nervous system (HADDERS-ALGRA, 2014), suggesting that it is one of the most predictive tools for early detection of brain dysfunction before the corrected age of five months (EINSPIELER; PEHARZ; MARSCHIK, 2016; EINSPIELER; PRECHTL, 2005; EINSPIELER et al., 1997; NOVAK et al., 2017). The evaluation of GMs using the Prechtl method classifies the GMs as: a) Writhing Movements, which can be "normal," "poor repertoire," "cramped-synchronized," or "chaotic"; and b) Fidgety Movements, which can be normal, abnormal, or absent (EINSPIELER; PRECHTL, 2005; EINSPIELER et al., 1997). Manipulation of the baby is not allowed during the assessment, and newborns are positioned in a supine position, wearing only diapers or short clothes that allow freedom of movement (EINSPIELER; PRECHTL, 2005). The evaluation lasts about 5 minutes and must be filmed for analysis

#### 4.7.2 Neonatal Neuromotor Screening (TNN)

A Neonatal Neuromotor Screening (TNN) was developed by Gonçalves (2012), based on the Dubowitz Neurological Signs Scale protocol (1970), and is used as a tool for the early diagnosis of neuromotor disorders in both term and preterm newborns (BIAZUS et al., 2016; GONÇALVES, 2010). It consists of 18 items and evaluates: posture, passive tone, active tone, primitive reflexes, and automatic body adjustment reactions. The application of the protocol should preferably be done when the baby is in an alert state, starting with the observation of posture, followed by the assessment of passive tone in the upper limbs, lower limbs, active tone, primitive reflexes, and alignment reactions. The final score is the sum of the scores obtained in each of the evaluated neurological signs items and is classified as hypotonia, normotonia, or hypertonia. The diagnostic conclusion is obtained by adding these scores along with the clinical data of the baby. It is easy to apply and takes, on average, 10 minutes, with the baby lying in the crib or examination table (GONÇALVES, 2012) (Figure 1)

| Sinais neurológicos         | RESULTADO                       |                           |                             |                           |                                  | OBS |
|-----------------------------|---------------------------------|---------------------------|-----------------------------|---------------------------|----------------------------------|-----|
|                             | 0                               | 1                         | 2                           | 3                         | 4                                |     |
| Postura                     |                                 |                           |                             |                           |                                  |     |
| Retorno à flexão dos braços | 
180°                        | 
90°-100°              | 
180°                    | 
90°                   | 
< 90°                        |     |
| Sinal de cachecol           | 
Mão ultrapassa ombro oposto | 
Mão toca ombro oposto | 
Mão chega mamilo oposto | 
Mão chega linha média | 
Mão chega mamilo ipsilateral |     |
| Retorno à flexão das pernas | 
180°                        | 
90°-100°              | 
180°                    | 
90°-110°              | 
< 90°                        |     |
| Ângulo poplíteo             | 
180°                        | 
130°                  | 
110°                    | 
90°                   | 
< 90°                        |     |
| Calcanhar-orelha            | 
180°                        | 
150°                  | 
130°                    | 
110°                  | 
90°                          |     |
| Dorsiflexão do Pé           | 
0°                          | 
20°                   | 
45°                     | 
75°                   | 
90°                          |     |
| Queda da cabeça             | 
                            | 
                      | 
                        | 
                      | 
                             |     |
| Suspensão ventral           |                                 |                           |                             |                           |                                  |     |
| Elevação de cabeça          | 
                            | 
                      | 
                        | 
                      | 
                             |     |

**Figure 1.** Illustration of the neurological signs of the Neonatal Neuromotor Screening. Source: Gonçalves (2012).

#### 4.7.3 Brazelton's Neonatal Behavioral State

The adapted Brazelton's Neonatal Behavioral Assessment Scale was used to assess behavioral state. The scale categorizes the newborn's behavior based on their current state,

ranging from 1 to 6. State 1: deep sleep, still with steady breathing; State 2: light or active sleep, eyes closed with occasional body movements; State 3: drowsy, intermittently opening and closing the eyes; State 4: quietly alert, minimal physical activity; State 5: fully awake with energetic movements (active alert); State 6: crying (BRAZELTON et al., 1976).

#### **4.7.4 Silverman-Andersen Score - BSA**

To quantify the degree of respiratory distress/discomfort and monitor its evolution, the Silverman-Andersen Score (BSA) will be used. This is a clinical method that helps estimate the severity of pulmonary impairment. The score is calculated by summing the points (ranging from 0 to 2) assigned to the following parameters: intercostal retraction, xiphoid retraction, nasal flaring, and expiratory grunting. A total score below 5 indicates mild respiratory difficulty, while a score of 10 indicates the maximum degree of pulmonary dyspnea (SILVERMAN; ANDERSEN, 1956; BRAZIL, 2011b) (Figure 2).

|   | Retração Intercostal                                                                                        |                                                                                                      | Retração xifoide                                                                                     | Batimento de asa nasal                                                                           | Gemido expiratório                                                                                             |
|---|-------------------------------------------------------------------------------------------------------------|------------------------------------------------------------------------------------------------------|------------------------------------------------------------------------------------------------------|--------------------------------------------------------------------------------------------------|----------------------------------------------------------------------------------------------------------------|
|   | Superior                                                                                                    | Inferior                                                                                             |                                                                                                      |                                                                                                  |                                                                                                                |
| 0 | [figure not shown]
Sincronizado         | [figure not shown]
Sem tiragem   | [figure not shown]
Ausente       | [figure not shown]
Ausente  | [figure not shown]
Ausente               |
| 1 | [figure not shown]
Declive inspiratório | [figure not shown]
Pouco visível | [figure not shown]
Pouco visível | [figure not shown]
Discreto | [figure not shown]
Audível só com esteto |
| 2 | [figure not shown]
Balancim             | [figure not shown]
Marcada       | [figure not shown]
Marcada       | [figure not shown]
Marcado  | [figure not shown]
Audível sem esteto    |

**Figure 2.** Illustration of the Silverman-Andersen Score. Source: Brazil (2011b).

## **4.8 Procedures**

### **4.8.1 Procedures of ethics and study registration**

The study will be submitted to the Ethics Committee of the Federal University of Mato Grosso do Sul, following the Guidelines and Regulatory Standards for Research Involving Human Beings (Res. 466/2012) from the National Health Council. Before the recruitment of subjects begins, the project will be registered in the Brazilian Clinical Trials Registry.

#### **4.8.2 Procedures of randomization and allocation**

The distribution of newborns into groups will be random, following a prior computational randomization in blocks of 4 babies for each group. The allocation to the groups will be concealed from the researchers involved through individual opaque, sealed, and sequentially numbered envelopes. The envelopes will be opened before the experimental or control protocol is performed, according to the inclusion of the babies in the study. The evaluations for GMs will be filmed and scored later, without identifying the allocation of the newborns in the groups, allowing for a subsequent blinded assessment.

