### **Abstract**

Preterm newborns are vulnerable to perinatal conditions due to their organic immaturity and associated external factors. This association can lead to neurological impairments, affecting motor development, respiratory mechanics, and the establishment of breastfeeding. Considering the current approach to the humanization of neonatal care, as well as the recent Brazilian epidemiological need for studies focused on early intervention in hospitalized newborns at risk or with established neurological problems, the necessity for therapeutic investigations that help prevent and minimize morbidities in this population becomes evident. The primary objective of this study is to evaluate the short- and medium-term effects of a physiotherapeutic intervention protocol associated with kangaroo positioning on the neuromotor behavior and clinical outcomes of preterm newborns in a neonatal unit. A randomized controlled trial with a parallel group design and balanced distribution ratio will be conducted. A total of 34 preterm newborns, with more than 72 hours of postnatal life and stable clinical conditions, admitted to Neonatal Intermediate Care Units will participate in this study. They will be randomly divided into two groups: a) Experimental Group (EG), which will receive the physiotherapeutic intervention protocol associated with kangaroo positioning; and b) Control Group (CG), which will receive only the kangaroo position. The protocol will be implemented over 10 consecutive days, with each session of the physiotherapeutic intervention lasting 15 minutes and 60 minutes of kangaroo positioning, during the period from 34 to 36 weeks and 6 days of postmenstrual age. Primary outcomes will include weight gain at the end of the protocol; Prechtl's general movements assessment at 36 weeks postmenstrual and 12 weeks post-term. Secondary outcomes will include posture and muscle tone, behavioral state, time to establish and maintain breastfeeding, duration of hospitalization, and vital signs. This study will provide experimental support for evidence-based practice, and its results may be used to guide feasible intervention protocols for the routines of neonatal unit teams in Brazilian hospitals.

**Keywords:** Early stimulation. Kangaroo method. Preterm newborn. Child development.

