### **4.2 Participants**

This study will involve 34 preterm newborns, born with a gestational age of 34 weeks or less, between 34 and 36 weeks and 6 days postmenstrual age, hospitalized in the Neonatal Intermediate Care Unit (UCIN). To estimate the minimum number of participants, considering a difference of at least 50% between the groups regarding the quality of general movements (GMs) after the intervention using the chi-square test, the suggested sample size is 13 participants per group (80% power;  $\alpha = 5\%$ ). Considering potential losses during the follow-up, two groups of 17 participants will be included. The newborns will be randomly allocated into two groups: the experimental group ( $n=17$ ), which will receive the physiotherapy intervention protocol associated with the kangaroo position, and the control group ( $n=17$ ), which will receive only the kangaroo position.

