### **4.3 Inclusion criteria**

Preterm newborns will be included in the study if they meet the following criteria: gestational age at birth equal to or less than 34 weeks, more than 72 hours of postnatal life, hospitalized in the Neonatal Intermediate Care Unit (UCIN), clinically stable, general

movements with a poor repertoire, no need for invasive or non-invasive mechanical ventilation, may require oxygen support via nasal cannula, residents of Campo Grande-MS (Brazil).

Medical records, nursing notes, physiotherapy records, and the recommendations from neonatologists and the multidisciplinary team will be used as the reference for the selection or exclusion of patients based on the criteria described above.

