#### *4.8.5.1 Physiotherapeutic intervention protocol*

The physiotherapeutic intervention protocol will be applied only to the experimental group. The intervention will consist of the following handling techniques: I) Lumbosacral pumping; II) Posterior stretching; III) Cervical muscle stretching; IV) Thoraco-humeral dissociation; V) Therapeutic exercise to feel the head with the hands; and VI) Positioning in supine to allow spontaneous movements of the preterm newborn. The protocol begins with lumbosacral pumping while the newborn is in a supine position with the head slightly flexed. The therapist's right hand is positioned on the lumbosacral region, and the left hand supports the anterior pelvic region. Using the right hand's middle and ring fingers, the therapist gently pulls in a caudal direction (GONÇALVES, 2012; BUSQUET-VANDERHEYDEN, 2009); without losing pelvic retroversion, the newborn is moved to a lateral position, and posterior stretching is performed with the right hand on the sacral region and the left hand positioned under the occipital bone, performing subtle, passive traction on both sides of the vertebral axis during expiration (LIMA, 2012; BUSQUET-VANDERHEYDEN, 2009). After this handling, cervical stretching is performed with the therapist's right hand holding the shoulder and the left hand supporting the occipital and temporal regions. The newborn is raised to approximately 30°, the head and neck are gently slid to the right side, while the left shoulder is softly lowered. The shoulder is released, and the head is returned to the midline. The hands are reversed, and the movement is performed on the opposite side (DUARTE et al., 2011); immediately after this handling, thoraco-humeral dissociation is performed, where the therapist uses one hand to hold the shoulder region and makes circular movements in a postero-anterior direction (LIMA, 2012); in the exercise to feel the head with the hands, the newborn remains in a supine position, with the cervical spine straightened, trunk and lower limbs flexed, and the newborn's hands are moved to the parietal region, sliding the palms of the hands forward and laterally over the face, rubbing them in front (DUARTE et al., 2011); to finish, the newborn will be positioned in a supine position in the incubator/crib, allowing spontaneous movements with the nest slightly away. The protocol will last 15 minutes, and immediately afterward, the newborn will be placed in the kangaroo position with the mother for 60 minutes.

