#### **4.8.3 Control protocol**

The newborns in the control group will undergo the same kangaroo positioning procedures described earlier but will not receive the physiotherapy intervention protocol. Thus, the newborn will be positioned in the incubator/crib before being placed in the kangaroo position with the mother.

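### A single fixed block size stated in the protocol, with visibly unblinded delivery, could make up to about a third of allocations predictable and so weakens the envelope concealment

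*Protocol*

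**What the plan says.** - **Sequence.** Section 4.8.2 describes allocation "following a prior computational randomization in blocks of 4 babies for each group". No other block size appears. The abstract gives a "parallel group design and balanced distribution ratio", and section 4.2 sets the numbers: "Considering potential losses during the follow-up, two groups of 17 participants will be included".
- **Concealment.** Section 4.8.2 specifies "individual opaque, sealed, and sequentially numbered envelopes". On timing it says: "The envelopes will be opened before the experimental or control protocol is performed, according to the inclusion of the babies in the study".
- **Visibility of treatment.** Section 4.8.5.1: "The physiotherapeutic intervention protocol will be applied only to the experimental group". Section 4.8.3 (Control protocol) says controls have the same kangaroo positioning but "will not receive the physiotherapy intervention protocol". No sham handling is described.
- **Entry.** Section 4.3 requires clinical stability among other criteria, and says that "the recommendations from neonatologists and the multidisciplinary team will be used as the reference for the selection or exclusion of patients". Section 4.4 adds contraindications to the handling or to the position.
- **Blinding.** Section 4.8.2 provides for general-movement films to be scored without knowledge of the group. No blinding is described for weight gain, the other primary outcome.
- **Sites.** Section 4.5 names two recruiting hospitals. The protocol does not mention stratification or a separate list per site, does not say who prepares or holds the list, and does not say whether recruiters are told the block size.

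**The concern.** Envelopes hide the next card, but they do not stop anyone deducing it. In a block of constant, known size, once one arm is full the rest of the block is determined. Earlier allocations are visible because only one arm receives hands-on therapy. Where entry leaves some judgement, as with clinical stability and contraindications, an infant could be put forward or held back, even unintentionally, when the next arm is known or suspected.

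The consequence would be arms that differ in prognosis at entry. Scoring films blind guards against biased measurement, not against biased enrolment, so general movements, weight gain, breastfeeding and hospital stay could all be affected. The block phrase is also ambiguous: it can mean four infants in total (2:2) or four in each arm (4:4, a block of eight), and predictability differs between the two.

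**Working it through.** The protocol gives no figure for predictability, so there is none to reproduce. Inputs: 34 infants at 1:1 (abstract, section 4.2); block of 4 or 8 (section 4.8.2, two readings).

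**1. Allocations known with certainty.** With m infants per arm in a block of 2m, the expected number known in advance is 2m/(m+1).

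- Block of 4 (m = 2): position 4 is always known. Position 3 is known when the first two match, which holds for 2 of the 6 possible sequences. The total is 1 + 1/3 = 4/3 of 4, or 33.3%.
- Block of 8 (m = 4): 8/5 = 1.6 of 8, or 20%.

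Over 34 infants:

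- Block of 4: 8 full blocks plus 2 infants (neither certain), 8 × 4/3 = 10.7, or 31.4%.
- Block of 8: 4 full blocks plus 2, 4 × 1.6 = 6.4, or 18.8%.

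**2. Best-guess accuracy** (always guess the arm with more places left in the block; 50% by chance).

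- Block of 4, positions 1 to 4: 1/2 + 2/3 + 2/3 + 1 = 17/6 of 4, or 70.8%. Over 34: 8 × 17/6 + (1/2 + 2/3) = 23.8, or 70.1%.
- Block of 8, by enumeration: 373/70 = 5.33 of 8, or 66.6%. Over 34: 22.4, or 65.8%.

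**3. Effect of varying the sizes** (simulation, 4,000 runs of 34, recruiter assumed to know the set of sizes but not their order).

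| Scheme | Known with certainty | Best guess correct |
|---|---|---|
| Fixed 4 | 31% | 70% |
| Fixed 8 | 19% | 66% |
| Random 4/6 | 6% | 69% |
| Random 4/6/8 | 2% | 68% |

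**4. Possible bias.** The documents give nothing from which to set this, so it is an assumption shown over a range. Suppose infants put forward under the two guessed arms differ in prognosis by d SD. If staff act on every guess with accuracy g, the expected difference between arms is (2g − 1) × d. If they act only on certain allocations (share c), it is c × d. The false-positive rate is that of a two-sided 5% t-test with 17 per arm (noncentral t, 32 df, noncentrality = bias × √(17/2)).

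| Scheme | Staff act on | d = 0.2 | d = 0.5 |
|---|---|---|---|
| Fixed 4 | every guess | 0.08 SD, 5.6% | 0.20 SD, 8.8% |
| Fixed 8 | every guess | 0.06 SD, 5.4% | 0.16 SD, 7.3% |
| Random 4/6/8 | every guess | 0.07 SD, 5.5% | 0.18 SD, 7.9% |
| Fixed 4 | certain only | 0.06 SD, 5.4% | 0.16 SD, 7.3% |
| Fixed 8 | certain only | 0.04 SD, 5.1% | 0.09 SD, 5.8% |
| Random 4/6/8 | certain only | under 0.01 SD, 5.0% | 0.01 SD, 5.0% |

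Varying the sizes removes almost all of the bias that comes from certain knowledge and very little of the bias that comes from guessing.

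**The case against.** A reader might infer that recruiting staff do know a third of the allocations, that the block size was published, and that the envelopes are therefore worthless. The documents support none of these.

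- They do not say that recruiters know the block size or keep a record of the order, nor who holds the list. Section 4.8.1 promises registration, not publication of the protocol during recruitment.
- Read literally, four for each group is a block of eight, and the certain share is then about a fifth.
- With two hospitals and no separate list per site stated, a shared list could be decoded only by someone who also followed the other hospital's sequence.
- Even at worst, about two thirds of allocations cannot be known for certain, and section 4.8.2 already ties envelope opening to inclusion.
- Section 4.3 makes the team's advice a means of applying listed criteria. Many of these are objective, such as gestational age, hours of life, ventilation and residence. The start is tied to reaching 34 weeks (section 4.8.5.2), which limits deferral.
- The bias figures rest on an assumed prognostic difference. At 0.2 SD the false-positive rate is close to nominal, and the remedy barely changes best-guess accuracy.

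All of this limits the size and certainty of the problem. What stands is that a constant block size is fixed in the researchers' own text, treatment is visible, and entry leaves some judgement. Predictability is therefore a stated design choice, not a detail left for a later document.

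**Conclusion.** The point holds in a conditional form. For someone who knows the block size and has followed all earlier allocations (at both hospitals, if they share one list), up to about a third of allocations are certain in advance with 2:2 blocks, and about a fifth with four per arm. This weakens the concealment without removing it.

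Any resulting bias cannot be fixed from the documents. For a block of 4 with staff acting on every guess, it runs from about 0.08 SD (false-positive rate 5.6%) at an assumed 0.2 SD prognostic difference to about 0.2 SD (about 9%) at 0.5 SD. These are illustrations of possible harm; they do not show that selection took place, and they should not be presented as removed by the fix. The remedy is worth making because it is cheap and because the block sentence needs clarifying anyway.

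**What to change.** 1. State in section 4.8.2 how the blocks are formed, so that four in total and four per arm can no longer be confused, and whether each hospital has its own list.
2. Have someone outside recruitment generate the list with randomly varying block sizes, for example 4, 6 and 8, and hold it. Keep the sizes out of the text that recruiters use.
3. As a clarification of what section 4.8.2 already implies, say that the envelope is opened only once consent, eligibility and baseline assessment are recorded as complete.

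**Cost.** A regenerated list and a few edited lines. The final split may miss 17:17 by a few infants. The present scheme does not guarantee 17:17 either: 34 is not a multiple of 4 or 8, and under blocks of 4 the last two infants fall in the same arm with probability 1/3, giving 18:16.

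**Limit.** The change cuts allocations known with certainty to about 2%. Best-guess accuracy goes only from about 70% to 68%, and if the present block is really 8 it is already about 66%, so on that measure nothing is gained.
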